## Introduction

Thoracoscopic surgery has emerged as the backbone of surgical procedures for lung resection in recent years, but these procedures still cause moderate-to-severe postoperative acute and chronic pain (1–4). Preemptive analgesia is regarded as a proven approach to minimize postsurgical pain (5). Several preemptive analgesia approaches have been employed in thoracoscopic surgery, including paravertebral block, intercostal nerve block, and thoracic epidural block (6). The erector spinae plane block (ESPB), a new inter-fascial plane block technique first described in 2016 for thoracic pain treatment (7), has the advantages of easy handling, high safety, and a good analgesic effect (8, 9). However, ESPB with a single dosage of currently available local anesthetics is limited by the short duration of analgesia (typically 24 h or less). The duration of analgesia can be prolonged by continuous peripheral nerve blocks using a perineural catheter; however, this may result in a variety of inconveniences and side effects, such as management complexity, catheter-related infections, leakage, and accidental dislocation (10, 11).

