Liposome bupivacaine (LB) is a novel local anesthetic with water-soluble bupivacaine wrapped in a liposome, allowing for a steady, continuous release of the drug for up to 72 to 96 h (12, 13). In 2011, liposomal bupivacaine was approved by the U.S. Food and Drug Administration to be used in single-dose wound infiltration for postsurgical analgesia in adults, and then the indication was expanded to transverse abdominis plane blocks and interscalene brachial plexus blocks (14, 15). Liposome bupivacaine appears safe when used in fascial plane blocks and peripheral nerve blocks (16–20). Whether LB is superior to traditional local anesthetics in postoperative analgesia after thoracic surgery remains controversial. Several retrospective studies have suggested that LB applied in minimally thoracic surgery improved postoperative pain, decreased opioid use, and shortened hospital stay in comparison with bupivacaine hydrochloride (HCl) (21–23). A recent randomized controlled trial including 50 patients undergoing minimally invasive lung surgery indicated that LB for intercostal nerve block provided no benefit in mitigating postoperative pain compared with bupivacaine plus epinephrine (18). However, that study had a smaller sample size and did not exclude the patients with more complex pain problems. To date, the analgesic efficacy of LB used in ESPB procedures on acute or chronic postsurgical pain remains unknown.

In this context, we designed this multicenter randomized controlled trial to determine the effect of LB versus bupivacaine HCl for preoperative ultrasound-guided ESPB on postoperative acute and chronic pain in patients undergoing video-assisted thoracoscopic lung surgery. In addition, we will also evaluate its safety profile when used in the ESPB procedures.

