### Postsurgical assessments

Pain intensity assessments are conducted at 0 h (~15 min after extubation), 1 h (± 10 min), 6 h (± 2 h), 12 h (± 2 h), 18 h (± 2 h), 24 h (± 2 h), 32 h (± 2 h), 40 h (± 2 h), 48 h (± 2 h), 60 h (± 2 h), and 72 h (± 2 h) postoperatively, and at patient’s request for rescue medication, where the time of the completion of surgery is considered 0 of the postoperative time. Pain intensity is assessed using an 11-point NRS (0 = no pain; 10 = worst possible pain) at rest and on activity; the latter refers to the scoring when turning over on bed if the subjects are still not out of bed for activity, or the scoring on active movement if the subjects are already out of bed. Telephone follow-up is performed if the subjects are discharged from the hospital within 72 h. During the nighttime (23:00 to 06:00, the next day), the subject is not awakened for scoring. If the subject is awake during the time window, the NRS score is assessed based on the subject’s own or companion’s recollection in the following morning; if the patient is asleep during the time window, the NRS score is standardized to a uniform value of 2. Considering the potential impact of opioid rescue medications on pain measurements, the windowed worst observation carried forward (wWOCF) method is utilized to accurately document NRS pain scores in the initial 72 h following surgery. The wWOCF approach operates in the following manner: to obtain the wWOCF for subjects who receive rescue medication, any NRS scores noted within a 2-h “window” following the administration of opioid rescue medication are replaced by the highest (“worst”) NRS scores recorded before the administration of their initial rescue medication. The time to the first rescue analgesia using PCIA was recorded, and the amount of medication used for rescue analgesia with the PCIA analgesic pump was also calculated. Quality of Recovery 15 (QoR-15) scores at 72 h after surgery are used to evaluate the subject’s recovery. NRS scores are measured once daily after 72 h postoperatively until study day 15. The number of continued days and the dosage of the oral analgesic drug celecoxib after discharge are also recorded.

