### Trial outcome definitions

#### Primary outcome

The primary outcome for the trial is the area under the curve of pain scores at rest for 0–72 h (AUC NRS-R_0-72_) postoperatively.

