### Sample size calculation

Between January 2023 and March 2023, we conducted a prospective study on two groups of 10 patients each. All participants underwent video-assisted thoracoscopic lung surgery and were administered a preoperative ultrasound-guided ESPB, with one group receiving liposome bupivacaine and the other bupivacaine HCl. The results showed that the postoperative AUC NRS-R0-72 was 247 ± 35 in the LB group versus 262 ± 43 in the BUPI group. Based on the preliminary study, the sample size was determined to ensure the ability to detect a mean difference of 15 in the primary efficacy outcome, and we suggest that this difference is clinically relevant. This calculation is performed with a two-group *t*-test, a standard deviation of 38.7, an 80% power, and a 0.05 level of significance. Considering a 20% dropout rate, this study will enroll a total of 272 patients, with 136 in each group. The sample size is calculated using the SAS software (version 9.4, SAS Institute Inc).

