Demographic information and baseline characteristics will be described using descriptive statistics only, with no between-group comparisons. Continuous data will be displayed as means and standard deviations or medians and interquartile ranges, depending on data distribution. Categorical data will be summarized as counts and percentages. Between-group differences of continuous data will be analyzed using the independent t-test or Mann–Whitney rank sum test as appropriate, while categorical data will be analyzed using the Chi-squared test or Fisher’s exact test as appropriate. To analyze the treatment effect, odds ratios are calculated for binary data and mean differences for continuous data, each together with their 95% confidence intervals. For the primary outcomes, the between-group difference of AUC NRS-R_0-72_ is regarded as significant at the two-side *p*-value of 0.05. For the secondary and tertiary outcomes, multiple comparisons are adjusted for the significance level of probability values by computing the false discovery rate using the Benjamini-Hochberg method. To further understand the cumulative effect of study interventions on postsurgical pain, *post-hoc* analysis is conducted, including AUC NRS-R_0-24_, AUC NRS-R_24-48_, AUC NRS-R_48-72_, AUC NRS-A_0-24_, AUC NRS-A_24-48_, and AUC NRS-A_48-72_, the cumulative amount of opioid rescue analgesics during 0–24, 24–48, and 48––72 h, and the proportion of subjects who are pain-free (NRS-R score of 0 or 1) at 1, 6, 24, 48, and 72 h. To address the missing NRS pain intensity scores during the postoperative 0–72 h, interpolation is performed using one of the following methods: (1) by last observation carried forward (LOCF) imputation method if missing data are located after the last non-missing score, (2) by linear interpolation if more than one missing data occur and are located between two non-missing scores (25). All data will be analyzed using the SAS software (version 9.4, SAS Institute Inc) by an independent statistician.

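### LOCF is the only stated rule for trailing missing scores in the primary 0–72 h AUC; its flat-pain assumption does not fit the trial's rationale and can bias the comparison

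*Protocol article*

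**What the plan says.** All references are to the Protocol article.

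- **Primary outcome:** "The primary outcome for the trial is the area under the curve of pain scores at rest for 0–72 h".
- **Postsurgical assessments:** eleven scheduled scores, at 0, 1, 6, 12, 18 and 24 h and then at "32 h (± 2 h), 40 h (± 2 h), 48 h (± 2 h), 60 h (± 2 h), and 72 h (± 2 h) postoperatively". Patients discharged before 72 h are scored by telephone.
- **Statistical analysis:** missing 0–72 h scores are filled by one of two rules. Gaps between observed scores are filled "by linear interpolation if more than one missing data occur and are located between two non-missing scores". Gaps at the end are filled "by last observation carried forward (LOCF) imputation method if missing data are located after the last non-missing score". The second rule has no condition on when or why the scores stop. Data from patients who withdraw consent are kept up to withdrawal, so their later scores become trailing gaps.
- **Introduction:** a single-dose block with current local anesthetics "is limited by the short duration of analgesia (typically 24 h or less", whereas the liposomal form is described as "allowing for a steady, continuous release of the drug for up to 72 to 96 h".
- **Sample size calculation:** a difference of 15, SD 38.7, 80% power and 0.05 significance. "Considering a 20% dropout rate, this study will enroll a total of 272 patients".

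**The concern.** LOCF is correct on average only if pain does not change after the last recorded score. The trial's rationale points the other way. If the conventional block fades within about a day while liposomal release continues, the arms should separate in the later part of the window, and 48 of the 72 hours lie after 24 h. Analgesia also changes by design within the window: celecoxib starts the day after surgery and PCIA stops after 48 h (Study interventions).

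A comparator patient whose last score falls while the block still works is given that block-level pain up to 72 h. The error need not be the same in the liposomal arm, so it need not cancel in the comparison.

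LOCF is also a single imputation. The filled-in scores enter the AUC, and then the t-test or rank test, as if observed, so the confidence interval does not reflect that they were guessed.

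The target is small, 15/72 = 0.21 NRS points averaged over the window, so modest distortions of the primary estimate count.

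**Working it through.** **1. The plan's own figure.** With difference 15, SD 38.7, two-sided 0.05 and 80% power:

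n = 2 × (1.96 + 0.84)² × 38.7² / 15² = 105 per arm (106 by the exact t-test).

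Dividing by 0.80 gives 132 or 133 per arm, 264 or 266 in total. The plan has 136 and 272. The pooled pilot SD, √((35² + 43²)/2) = 39.2, gives 108 or 109, and 135 or 137 after inflation. The plan's size is reproduced to within 3%.

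**2. Late-difference scenario (assumed).** No difference through 24 h and a constant difference d from 32 h on. By the trapezoid rule on the protocol's grid, the interval 24–32 h contributes 4d and 32–72 h contributes 40d. So 44d = 15 and d = 0.341 NRS points.

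**3. LOCF in that scenario.** Let a share m of each arm have its last score at or before 24 h. LOCF carries forward a difference of zero for these patients, so

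expected difference = (1 − m) × 15 + m × 0.

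Power = Φ(difference / (38.7 × √(2/n)) − 1.96), with SD held at 38.7. The standard error is 4.69 at n = 136 and 5.24 at n = 109 (136 × 0.80).

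| Share m (assumed) | Expected difference | Power, 136 per arm | Power, 109 per arm |
|---|---|---|---|
| 0 | 15.0 | 0.89 | 0.82 |
| 5% | 14.25 | 0.86 | 0.78 |
| 10% | 13.5 | 0.82 | 0.73 |
| 20% | 12.0 | 0.73 | 0.63 |

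The 136 column fits if LOCF keeps everyone in the analysis. The 109 column fits if 20% are lost altogether and the share m applies to those who remain.

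**4. Other assumed patterns, each scaled to a true difference of 15.**

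- Same late-difference curve, last score at 32 h or later: 15.0, no bias.
- Constant difference over the whole 72 h: 15.0, no bias.
- Difference starting after 12 h, half size at 18 h and full from 24 h; last score at 18 h in 20%: 0.8 × 15 + 0.2 × 7.92 = 13.58.
- Difference full at 32–48 h, half at 60 h and zero at 72 h; last score at 48 h in 20%: 0.8 × 15 + 0.2 × 20.62 = 16.12. The effect is overstated.

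**5. Missingness that differs by arm.** Suppose resting pain falls linearly from 4.5 to 2.5 over 72 h. Carrying the 24 h score forward adds ½ × 48 × (48 × 2/72) = 32 AUC units per affected patient. A 5 to 10 percentage-point imbalance between arms shifts the contrast by 1.6 to 3.2 units, against the arm with more gaps. From 48 h the addition is ½ × 24 × (24 × 2/72) = 8 units, and the shift is 0.4 to 0.8. If pain instead rose from 3 to 4, the 24 h figure would be −16 units and the shift would reverse, to 0.8 to 1.6 in favor of that arm.

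**The case against.** The strongest reply is that few patients may be affected. Early discharge, an obvious source of trailing gaps, is covered by telephone scoring, and a patient asleep at a night-time assessment receives an assigned score. What remains is mainly withdrawal of consent and failed telephone contact, and the article gives no rate for either. This stands, and it limits the likely size. It does not make the rule suitable for the patients to whom it applies.

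Three stronger readings are tempting, and the article does not support them.

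- *That the primary effect is certain to be biased, with the AUC frozen at block-period pain.* This applies only to patients last scored at or before about 24 h. Five of the eleven scheduled times are at 32 h or later, after the conventional block's stated duration. The article does not state that the arms diverge after 24 h; that is inferred from its rationale. It gives no pain curve for either arm, so flat pain under the liposomal form is not established either: the Discussion describes a second release peak at 12 to 48 h.
- *That 20% is the rate of trailing missing scores.* It is a planning allowance for dropout. It serves above only as an upper scenario.
- *That a full NRS point of late separation can be set against the 15-unit target.* One point over 48 h is itself a true difference of about 48 units. With 10% missing, LOCF would remove 4.8 of those 48 and leave 43.2, with power near 100%. For a true difference of 15 the loss is 1.5.

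Finally, sensitivity analyses are commonly left to the analysis plan, which is not shown, so their absence from the article is not part of this point. The point is the primary rule that the article does fix.

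**Conclusion.** The point holds as a badly chosen primary rule. LOCF without limit is the only stated treatment of trailing missing scores in the primary AUC. It rests on a flat pain course that the trial's own rationale does not support, and it understates uncertainty.

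The size cannot be fixed from the article, because neither the rate nor the timing of trailing gaps is given. When the difference arises wholly after 24 h and missingness is equal in both arms, the proportional loss of effect equals the share of patients last scored at or before 24 h: 5% to 20% over the assumed range. That bias is toward the null. It costs power and does not create a false benefit. The direction is not assured in general: it can be nil, or favor the liposomal arm if the difference fades late or gaps are unbalanced between arms. The change is worth making, but the article does not show that the trial's result will be materially wrong.

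**What to change.** In Statistical analysis, replace LOCF as the primary rule for trailing missing 0–72 h scores with multiple imputation. Impute the individual scores separately by arm, using all observed scores, rescue use and site. Form the AUC in each completed data set, then combine the estimates by Rubin's rules. This lets each arm follow its own course and carries the imputation uncertainty into the interval.

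Keep LOCF as a sensitivity analysis. Add a delta-adjusted or reference-based analysis, since multiple imputation itself assumes that the missing scores are predictable from the observed data.

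Report by arm how many patients have trailing gaps and the time of their last score, so that readers can judge how much the choice matters.

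The cost is analysis wording and programming, with no new data or patients. Study design and status says that the follow-up data stay locked until the final analysis, so the change can be dated and documented before unlocking.

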## Discussion

This multicenter, randomized, double-blind, parallel-controlled trial will include 272 subjects who will undergo elective video-assisted thoracoscopic lung surgery. We will determine the effect of LB versus bupivacaine HCl for preoperative ultrasound-guided ESPB on AUC NRS-R_0-72_, the amount of opioid rescue analgesics after surgery, time to the first rescue analgesia, AUC NRS-A_0-72_, NRS scores at rest and on activity at different time points during the 0–72 h postoperative period, and NRS scores on activity on postsurgical day 14 and postsurgical 3 months. Our primary hypothesis is that the use of LB for ultrasound-guided ESPB preemptive analgesia provides a lower area under the curve of pain scores at rest 0–72 h postoperatively compared to bupivacaine HCl. Moreover, we will explore the adverse events associated with the application of LB for ultrasound-guided ESPB. The administration of this trial and the presentation of results will follow the Consolidated Standards of Reporting Trials guidelines.

Regional nerve block maneuvers before skin incisions are considered an optimal method of preemptive analgesia, which facilitates the reduction of postsurgical pain. ESPB is a novel interfascial regional anesthesia technique first introduced by Forero et al. in 2016 for thoracic neuropathic pain treatment and has rapidly gained prevalence in a diverse range of surgical procedures (7, 26). In particular, it is easy to implement owing to the simple identification of anatomic landmarks on ultrasound and the fact that no vital organs are nearby (27). Anatomical and radiological investigations in fresh cadavers have suggested that the clinical effects of ESPB are likely derived from the theoretical anterior distribution of the local anesthetics through the intertransverse connective tissue or the costotransverse foramen to infiltrate the ventral crus of the spinal nerves, the dorsal root ganglion, and the sympathetic chain, thereby resulting in an effect similar to epidural analgesia (7, 28).

Recent studies have demonstrated that ESPB is a simple, safe, wide-ranging, and efficacious alternative analgesic technique for postsurgical pain (7–9, 29). A recent meta-analysis including 14 studies indicated that ESPB significantly lowered pain scores at rest or on movement, decreased 24 h opioid consumption, and reduced the incidence of postoperative nausea and vomiting compared with the non-block care in breast and thoracic surgery (30). Another meta-analysis also suggested that ultrasound-guided ESPB could provide an opioid-sparing effect in subjects undergoing surgeries with general anesthesia, thereby reducing the adverse events related to opioid administration, such as nausea, vomiting, and delayed peristalsis (29, 31, 32). The currently prevalent regional nerve block maneuvers in thoracoscopic surgery involve paravertebral and intercostal nerve blocks. Each of these procedures has its unique strengths and inherent disadvantages. For instance, paravertebral block is performed close to the spinal canal and vascular plexus, with technical complexity and potential risk of serious complications, while the effectiveness of intercostal nerve block may be limited to a dermatomal extent (33). Given the combination of its efficacy and lower associated risks, ESPB has been preferred in our study.

Liposomal bupivacaine (Bupivacaine Liposome Injection; Jiangsu Hengrui Pharmaceuticals Co., Ltd.; China) is a novel liposome-encapsulated local anesthetic used for surgical site administration to yield postsurgical analgesia. The delivery of local anesthetics using encapsulating agents is a desirable alternative, as it provides a system for sustained release and subsequently enhances analgesia (34). Liposomal bupivacaine has been shown to provide postsurgical analgesia with a similar safety profile to bupivacaine HCl in a variety of surgical scenarios, such as hemorrhoidectomy, total knee arthroplasty, mammoplasty, and thoracic surgery (18, 35–37). Liposome bupivacaine appears safe when used in fascial plane blocks and peripheral nerve blocks, such as ESPB, paravertebral block, and intercostal nerve block (16–20, 23).

However, evidence of the clinical effectiveness of interfascially or perineurally applied liposomal bupivacaine in extending the duration of postoperative analgesia of nerve blocks is insufficient. Several retrospective studies have demonstrated the superiority of LB over bupivacaine HCl in controlling postsurgical pain when the paravertebral blocks or intercostal nerve blocks are applied in thoracic surgery (21–23). Another retrospective study included 387 patients receiving either liposomal bupivacaine for an intrathoracic intercostal nerve block or thoracic epidural bupivacaine HCl in video-assisted thoracoscopic surgery (38). Liposomal bupivacaine used for the regional block was comparable with bupivacaine HCl for epidural analgesia, taking into account healthcare costs and analgesia efficacy. A randomized controlled trial compared the analgesic efficiency and safety of single-dose transversus abdominis plane (TAP) blocks with liposomal bupivacaine and sustained epidural analgesia, with bupivacaine HCl in 498 subjects undergoing major abdominal surgery (39). The results showed that pain scores at rest during the initial postsurgical days were similar between groups. Compared to subjects receiving epidural analgesia with bupivacaine HCl, those who received TAP blocks with liposomal bupivacaine required more opioid medication but had fewer complications, such as hypotension. Another randomized controlled study with a non-inferiority design that enrolled 112 patients undergoing ambulatory shoulder surgery demonstrated that interscalene nerve blocks with perineural LB offered similarly effective analgesia as the perineural standard bupivacaine with dexamethasone (40). A recent meta-analysis also suggested that perineural liposomal bupivacaine provided a statistically significant but clinically unconsidered improvement in the area under the curve of postoperative pain scores compared to plain local anesthetic (41, 42).

The variations in study protocols and injection site locations could influence study results. The pharmacokinetics profile of liposomal bupivacaine is apparently related to the duration of regional blocks (43). Liposomal bupivacaine exhibits a biphasic model, dose-related release profile with an initial peak release within 1 h of execution related to extra liposomal bupivacaine included in every ampule, followed by a further peak 12 to 48 h later, associated with the release from the liposomes (13, 44). Hence, preemptive analgesia with liposomal bupivacaine has the potential to reduce postoperative pain intensity. Furthermore, the rate of bupivacaine release from liposomes is speculated to be related to the vascularity of the surrounding tissue at the injection site. For example, approximately 30% of bupivacaine is released during the first 24 h when it infiltrates directly into tissues in knee replacement, and approximately 90% in more vascularly distributed hemorrhoidectomy (45). The erector spinae plane does not have a rich vascular plexus, and the rate of bupivacaine release from liposomes may be similar to other fascial plane blocks, allowing for prolonged anesthetic duration. More studies are warranted to determine the exact features and effectiveness of this block in various surgical procedures. To date, this is the first randomized controlled study to determine the efficiency of liposomal bupivacaine for ESPB on postoperative pain in thoracic surgery.

In this study, we formulate certain rules for NRS scoring to achieve multicenter consistency and eliminate the influence of external factors on pain outcomes. For instance, we have implemented the wWOCF protocol for recording NRS pain intensity scores in the first 72 h after surgery. This method is designed to reduce the influence of opioid rescue medications on the NRS evaluations. Specifically, if patients receive rescue medication within a 2 h “window” before an assessment, we will replace the score for that time point with the highest (“worst”) NRS score recorded before the administration of the initial rescue medication. In addition, we employ a nocturnal recall score to minimize the disruption to the patient’s nighttime rest. We do not take bedside face-to-face scoring at night (23:00 to 06:00, the following day). If the subject is awake within the time window, the subject or companion recollects the pain state the following morning, and if the subject is asleep during the time window, the NRS score is assigned a uniform value of 2.

Our study has several limitations. First, partial subjects were discharged within 72 h after surgery, and NRS scores for these subjects could only be followed up by telephone. Second, adverse events are only tracked up to the 7th postsurgical day without further follow-up. Finally, varying durations of oral analgesic medications or non-protocol analgesics may interfere with the NRS scoring for pain.

In conclusion, this randomized clinical trial was designed to determine the effect of liposomal bupivacaine versus bupivacaine HCl for preoperative ultrasound-guided ESPB on postoperative pain in video-assisted thoracoscopic lung surgery. We expected that liposomal bupivacaine could be safely employed in ESPB, and liposomal bupivacaine for preoperative ultrasound-guided ESPB would be more effective than bupivacaine HCl in reducing the area under the curve of pain scores at rest from 0 to 72 h postoperatively.

